## Methods

### Trial design

The project is a multicentre cluster randomized controlled trial (CRCT). Each participating geriatric unit, with responsibility to provide medical care to acutely admitted older medical patients, constitutes one cluster and is the unit of randomization. Figure 1 gives an overview of the study design. The article conforms to the Standard Protocol Items: Recommendations for Interventional Trials (SPIRIT) [36] (Additional file 1), and the study results will reported in accordance with the Consort 2010 extension to cluster randomized trials. All methods carried out in the study will be performed in accordance with relevant guidelines and regulations.

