The units were sorted from one to 12 according to the number of geriatric beds and then stratified into three strata: four clusters with 16 to 23 beds, six clusters with 6 to 10 beds and two clusters with 4 and 5 beds respectively. In each block, the clusters were randomized to either the intervention or the control arm with an allocation ratio of 1:1. An independent professor in epidemiology performed the allocation using the Microsoft Excel RAND-function, only knowing the numbers of the clusters. The randomization was performed to achieve a balance in unit types in the intervention and control arm and a similar size of the two arms including a similar number of admitted patients filling the inclusion criteria. All hospitals are located in cities or towns. The purpose of the stratification was primarily to achieve a balance in the number of patients and next of kin between the two arms, and secondly to include units of various sizes in both.

The study has primary outcomes for the implementation and for the clinical effectiveness. The primary outcome for the implementation outcome sub-study is the differences in fidelity changes between the arms. The unit of analysis for the fidelity scores is the health care units or clusters. Fidelity is rated on 5-point scales (1 = poor fidelity, 5 = high fidelity). Based on previous research (mean difference 1.82 and average SD 0.80 after 18 months with implementation support), we have calculated that we need at least four clusters in each arm to show that implementation support gives a significant increase in fidelity, based on 5% two-tailed significance and 80% power. If the differences are smaller in our study, we will need a larger sample. Due to the possibility of unit drop-out during the project period and to secure sufficient power, we have included six units in the intervention arm and six in the control arm.

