The primary outcomes for the clinical effectiveness study “The triadic sub-study with patients, next of kin and clinicians” are described under “outcomes”. The unit of analysis is the individuals recruited in each cluster. Since we have not found comparable studies that have published data on these instruments, we decided to use a 0.5 SD improvement (medium effect) when calculating the sample size. Based on a 0.5 SD increase in the primary outcome and an Intra-class Correlation Coefficient (ICC) of 0.05, we need 132 patients in each arm or 22 per cluster with six clusters in each arm to achieve 80% power to detect a difference in the primary outcome among patients, between groups with a certainty of 95%. Taking into account the possibility of patients in the control arm receiving ACP, and incomplete or missing data, we aim to recruit at least 35 patients per cluster. A similar power calculation with the same conservative assumptions has been done for the primary outcomes for next of kin and clinicians with the same results (35 next of kin and 35 clinicians per cluster).

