#### Data analysis

Demographic and clinical data about the patients will be used to assess whether the patients in the control and intervention units are comparable. In addition, the participating units will collect basic and anonymous clinical information about all patients admitted to the units at shorter random time periods, to get more information about the participant units and to compare the included patients with all admitted patients.

Number and percentages of invitation to and participation in ACP for patients and next of kin will be calculated and compared between intervention and control group. The primary statistical analyses will be the difference in mean outcomes between participants in the intervention and the control group using linear mixed effects models. The random part of the model will consist of random intercept for patient or relative identification nested within centre. Missing data will be handled by multiple imputation using predictive means matching with 100 imputed data sets.

If the analyses show differences in the intervention and control arm, we will perform analyses to assess if higher fidelity score (higher levels of implementation) is associated with improved outcomes for patients, next of kin, and clinicians. For the secondary outcomes, we will compute average outcomes and SD for the intervention and the control group and use the t-test to determine if there is a significant difference between groups.

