#### Data analysis

For the baseline data, we will perform descriptive analyses, and compute average outcomes and SD for the intervention and the control group and use the t-test to determine if there is a significant difference between groups. For the follow-up-data we will compute average outcomes and SD for each point of time and treatment group and test the mean difference in change between the intervention and the control group from baseline to 18 months using t-tests.

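### Secondary triadic outcomes and staff-survey outcomes are to be compared by two-group t-tests that make no allowance for the 12 randomised units, so their type I error exceeds 5% at any positive ICC

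*Protocol article*

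**What the plan says.** Under Trial design, the protocol article states that each geriatric unit "constitutes one cluster and is the unit of randomization". Under Selection, allocation of clusters and sample size it adds that "we have included six units in the intervention arm and six in the control arm". For the triadic sub-study the same section says "The unit of analysis is the individuals recruited in each cluster", and its sample size rests on a 0.5 SD difference and "an Intra-class Correlation Coefficient (ICC) of 0.05".

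The Data analysis section of the triadic sub-study gives the primary outcomes a linear mixed model with centre in its random part. For the other outcomes it changes method: "For the secondary outcomes, we will compute average outcomes and SD for the intervention and the control group and use the t-test to determine" whether there is a significant difference between groups.

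The Data analysis section under Questionnaires to all staff prescribes t-tests twice: for the baseline difference between arms, and at follow-up to "test the mean difference in change between the intervention and the control group from baseline to 18 months using t-tests". Neither section attaches a unit term, a unit-level summary or a design-effect correction to these tests.

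**The concern.** When whole units are randomised, patients, relatives, clinicians and staff of the same unit tend to answer alike. A two-group t-test on individuals treats them as independent, so its standard error is too small, its confidence interval too narrow and its p-value too low.

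The protocol recognises this for its primary triadic outcomes, in the sample size and in the model, but not for the comparisons named here. They carry much of secondary objective 6 (other outcomes for patients, next of kin and clinicians) and the between-arm comparisons for objective 8 (staff perceptions, attitudes, self-efficacy and confidence). The questionnaires cover many dimensions in several respondent groups, so an inflated error rate would apply to a long list of results.

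**Working it through.** **Inputs from the protocol article.** Six units per arm; 0.5 SD; ICC 0.05; 80% power; 95% certainty (two-sided 5% taken, as stated for fidelity); 22 patients per unit required and 35 per unit targeted (420 in total); 300 staff respondents in 12 units.

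**Assumptions.** Equal unit sizes, so 300/12 = 25 staff per unit; a 5% level for the secondary and staff tests; ICC 0.05 carried over to these outcomes, then varied.

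**1. The plan's own figure.** Without clustering, n per arm = 2(1.96 + 0.84)²/0.5² ≈ 63. The design effect is DE = 1 + (m − 1) × ICC. At m = 22, DE = 1 + 21 × 0.05 = 2.05. Then 63 × 2.05 = 129.15 per arm, and 129.15/6 = 21.5, rounded up to 22 per unit, or 132 per arm. This matches the protocol: "Based on a 0.5 SD increase in the primary outcome and an Intra-class Correlation Coefficient (ICC) of 0.05, we need 132 patients in each arm". So the protocol's own calculation treats the variance of the arm difference at this size as about twice that under independence.

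**2. Type I error of a t-test that ignores unit.** The true standard error is √DE times the one the test uses, so the actual error is 2 × [1 − Φ(1.96/√DE)].

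| Comparison | m per unit | DE at ICC 0.05 | √DE | Type I error | Simulated |
|---|---|---|---|---|---|
| Triads, required number | 22 | 2.05 | 1.43 | 17.1% | 17.2% |
| Staff | 25 | 2.20 | 1.48 | 18.6% | 18.6% |
| Triads, target | 35 | 2.70 | 1.64 | 23.3% | 23.3% |

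The simulation used 20,000 trials per row, 6 + 6 units and no true effect.

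**3. Range over the ICC.**

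| ICC | m = 25 | m = 35 |
|---|---|---|
| 0.01 | 7.8% | 9.0% |
| 0.02 | 10.7% | 13.0% |
| 0.05 | 18.6% | 23.3% |
| 0.10 | 28.8% | 35.0% |

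The error equals 5% only at ICC 0 and is above it for any positive ICC.

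**4. Unequal unit sizes.** The protocol reports units from 4 to 23 geriatric beds. With illustrative sizes per arm of 50, 40, 25, 15, 15, 5 (300 staff) and 70, 55, 30, 25, 20, 10 (420 triads), both assumed, the simulated error at ICC 0.05 is about 23% and 29%.

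**5. A test that respects the units.** In the equal-size simulations, a t-test on unit means with 12 − 2 = 10 df gave 4.9%, 4.7% and 5.0% at m = 22, 25 and 35.

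**6. Effect on interval width.** With 10 df the critical value is 2.228 instead of 1.96, a ratio of 1.137. Staff: 1.48 × 1.137 ≈ 1.7. Triads at 35 per unit: 1.64 × 1.137 ≈ 1.9.

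**The case against.** **The ICC is not stated for these outcomes.** This stands. A reader might take 18-23% as following from the protocol's own ICC, but 0.05 is given for the triadic primary outcomes only. For staff change, stable differences between units cancel, and the ICC of the change could be lower or higher than 0.05. The percentages are therefore conditional and need the range above. The direction does not depend on the value.

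**The numbers per unit may be smaller.** This also stands in part. The target of 35 allows partly for missing data, and at 22 the figure is 17%. A reader might also infer that the staff change test uses only people who answered at both times. The staff section does not say whether answers are linked, so that cannot be claimed. If, as an assumption, only 15 per unit entered, DE = 1 + 14 × 0.05 = 1.70 and the error would be about 13%.

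**The t-tests might be meant on unit means.** The text points the other way for the triads, whose unit of analysis is the individual. The staff section speaks of averages and SDs by time point and treatment group. Where the cluster is the unit of analysis, as for fidelity, the protocol says so.

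**A separate analysis plan may settle it.** A plan not shown could do so, but this is not silence in a condensed article: the article names a test. By contrast, the article's failure to mention a unit term in the total-cost regression is only silence, and no defect can be inferred from it.

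**Only secondary results are touched.** Correct. The primary triadic model includes centre, the fidelity t-test has the unit as its unit of analysis, and the fidelity subscales use mixed models with cluster intercepts.

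**Conclusion.** The plan is wrong as written for the secondary triadic outcomes and for both staff comparisons, baseline and change. Followed literally, it gives standard errors that are too small in a trial with 12 randomised units.

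If ICC 0.05 is assumed to apply, the type I error per test is about 23% at 35 triads per unit, 17% at 22, and about 19% at 25 staff per unit. For 25 to 35 per unit it runs from 8-9% at ICC 0.01 to 29-35% at ICC 0.10. These figures assume equal unit sizes. Unequal sizes raise them; the stratification by bed number, which is left out here, could lower them somewhat if bed number explains differences between units.

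A reader might infer that many of these results will be falsely significant, or that the trial's main conclusions are at risk. The documents support neither: the first depends on ICCs that are not given, and the primary triadic and fidelity analyses are outside this point.

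**What to change.** Replace the t-test sentences in the two Data analysis sections.

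- **Secondary triadic outcomes:** a linear mixed model with arm as fixed effect, an explicitly stated random intercept for hospital unit and a small-sample df correction; or a t-test on unit means with 10 df. State the unit intercept rather than only refer to the primary model, whose random part is described as a participant intercept nested in centre.
- **Staff survey, change:** a mixed model with arm, time and arm × time, a random intercept for unit and the same df correction, plus a respondent intercept if answers are linked over time; or a t-test on unit-level mean changes.
- **Staff survey, baseline:** any between-arm comparison should likewise carry the unit intercept or use unit means.

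The cost is analysis wording only: no new data, sites or participants. At ICC 0.05, confidence intervals become about 1.7 (staff) to 1.9 (triads) times wider than those from the planned t-tests. That is a real loss of apparent precision, but it is the width the design supports.

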### Questionnaires to all staff

In this sub-study we will invite all health care personnel and leaders who are eligible from all participating intervention- and control units. The inclusion criteria are health care personnel (medical doctors, nurses, care workers, occupational therapists, physiotherapists, speech therapists), and leaders employed or attached to the unit in a 20–100% position.

#### Data collection and outcomes

A digital questionnaire based on validated questionnaires [41, 43, 61] will be administrated at baseline and 18 months after the start of the intervention. This will provide data both to investigate the status at baseline and to evaluate possible differences in changes between the two study arms. The questionnaire includes the following dimensions:Patients’ and next of kins’ preferences for information and involvementWhether information, involvement and health care provided is concordant with the patients’ and next of kins’ preferences and reasons for discordanceDecision making authority – clinical realities and idealsSelf-efficacy and confidence in ACP-relevant information and involvement tasksDemographic information about the participants

#### Data analysis

For the baseline data, we will perform descriptive analyses, and compute average outcomes and SD for the intervention and the control group and use the t-test to determine if there is a significant difference between groups. For the follow-up-data we will compute average outcomes and SD for each point of time and treatment group and test the mean difference in change between the intervention and the control group from baseline to 18 months using t-tests.

### Qualitative evaluation of ACP and of the implementation support

After 14–16 months of implementation support, we will perform focus group interviews with health care personnel in the intervention units and focus group interview with each implementation team in the intervention units. From month 4 to 14, we will conduct individual interviews with 10–12 patients and 10–12 next of kin who have participated in ACP. Through these interviews, we will get in-depth data relevant to all the secondary objectives, and in particular 3, 4 and 5: Barriers to, facilitators for and experiences with implementing ACP, including moral dilemmas and conflicting interests related to ACP, and benefits and disadvantages related to ACP and the implementation support. For patients and next of kin, we will also explore experiences with information, involvement in decision making and satisfaction with the health services, for health care personnel we will also explore attitudes, confidence and competence in giving information to and in the involvement of patients and their close relatives when the patient is approaching the end of life.

The qualitative data will also be used in the responsive evaluation process, together with input and notes from network meetings with the local coordinators, trainers, and managers in the intervention units when they share their experiences on the same main topics explored in the interviews. We expect that implementing ACP involves multiple and complex barriers (e.g. prioritisations, the risk of over- and under treatment, differences in stakeholder perspectives and beliefs, who should decide what). After identifying key barriers and facilitators, we will include these findings in the training program and didactic material (web-based and paper-based), and – together with the stakeholders – we will develop and refine relevant tools to handle barriers that may prevent ACP. One example is a deliberation method, developed by the researchers in this project, which can be used to better handle dilemmas related to end-of-life care and shared decision-making [62]. The training and tools developed will be evaluated as an important part of the implementation intervention.

### Qualitative evaluation of barriers and facilitators for ACP in a broader context

The first qualitative sub-sub-study on barriers and facilitators in a wider health care service context was performed at baseline to inform the project and the development of the implementation strategy. Informants with special knowledge or experience with ACP or similar interventions were selected through a combination of a purposeful and snowballing method. Of 40 health care professionals and chief physicians in hospitals and community services, three had practiced ACP. Policy development, public and professional education, and standardization of documentation were reported as key factors to facilitate ACP and build trust across the health care system [53].

The second qualitative sub-study of ACP in a broader context is based on interviews conducted between May 2022 and June 2023, among stakeholders responsible for, or who may give important input to ACP policymaking and large-scale implementation of ACP at the municipal, regional and national level. We conducted a total of 15 interviews with health politicians on a national level, national health authorities, high-level leaders in both the hospital and municipal health care system, professional associations, user- and interest organizations, as well as leaders of health care educations. Relevant topics may be formal factors such as policy formulation, regulatory frameworks, financial arrangements, health educations, or other overarching structural incentives and barriers, and informal factors such as power relationships, conflicts of interest, knowledge traditions, norms, and values, coordination and collaboration across health care services, and barriers and facilitators within the various health care services at the organizational or clinical level.

#### Qualitative data analysis

For all the qualitative sub-studies we use semi-structured interview guides adapted to each stakeholder group. All interviews will be recorded and transcribed verbatim. The main analytic strategy will be a thematic analysis inspired by Braun and Clarke [63, 64], using the topics and questions in the interview guide as a starting point for the analyses, as well as relevant theories from implementation and social science, ethics, and relevant policies.

### Health economics

The economics analysis includes estimation of healthcare utilization, costs and cost-effectiveness of ACP and the implementation support in geriatric hospital units compared to standard of care. We will identify the resource use and costs related to implementing and conducting ACP in clinical practice, and we will estimate patient’s healthcare utilization and costs in order to identify differences in pathways as a result of implementation of ACP. Higher costs after implementation may indicate underutilization and lower costs may indicate overutilization of healthcare without ACP. The information on healthcare utilization will be collected from national registries covering both pharmaceuticals and primary, secondary, home based and institutional based care.

Resource use and healthcare utilization will be summarized over 18 months prior to inclusion in the trial and 18 months after. Total costs will be calculated, and we will use regression analysis to estimate the effect of ACP on total costs, also adjusting for individual characteristics, such as age, gender, comorbidity, living situation, social network, marital status and education measured at inclusion. We will also estimate the cost-effectiveness of implementation of ACP compared to standard of care. The costs will include intervention costs of ACP and the cost of the hospital stay. Differences in costs will be compared to the primary outcomes (measured as percentage point difference in quality of communication and decision-making for patients and for next of kin, congruence (attending clinicians) and fidelity (implementation outcome) and selected secondary outcomes. We will use the incremental cost-effectiveness ratio, defined as differences in costs between implementation of ACP compared to standard of care divided by percentage difference in primary (selected secondary) outcomes (ACP and standard of care). Uncertainty will be estimated by bootstrap methods and displayed in a cost-effectiveness plane.

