#### Patient outcomes

##### Questionnaire

Patients in the triadic sub-study will be asked to answer a short questionnaire including the following dimensions:Quality of communication and decision-making for the patient and the next-of-kin when approaching the end of life (primary outcome for patients)Communication about preferences for information and involvement, health care personnel’ current compliance with these preferences, and trust in future complianceSatisfaction with information about the patient’s state of health, discharge, prognosis, and future health care needs, and with information and involvement concerning health care provided during and after admittanceSelf-efficacy in communicating with next-of-kin and health care professionals about future deterioration, about preferences for life-prolonging treatment in such a situation, and about health care when approaching the end of lifeProblem causing admittance being solved; satisfaction with arrival, stay, and discharge at the hospital; and trust in necessary health care in the futureConcrete preferences for information and who should participate in important decisions about health care, and assessment of the amount of information givenGeneral life satisfaction [48]Demographic information

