##### Data from patient health records

The researchers will retrospectively go through the patients’ electronic health records, given sufficient project resources. We will collect documentation from 18 months before to 18 months after inclusion (or until death) on the following: ACP and other similar conversations, palliative care plans, life prolonging treatment and palliative care given, any decisions to limit such treatment or care, and the patients’ life stance or religious beliefs.

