##### Data from national registries

The patient dataset will be coupled to individual data from national registries (from 18 months before to 18 months after inclusion (or until death). This allows description of the patient population and their use of health services, and to assess possible long-term effects of ACP. The registers include the Norwegian Registry for Primary Health Care, Norwegian Patient Registry, Norwegian Prescription Database and Norwegian Cause of Death Registry.

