#### Recruitment

A local research coordinator at each participating unit will recruit participants assisted by the health care personnel at the units, guided by a set of instructions and supervision by the researchers. All potential participants will be assessed for eligibility. The patients who fulfil the criteria will receive verbal and written information about the study from a health professional at the unit. If a written informed consent is obtained, the health professional will ask the patient for permission to contact the closest relative to inform and possibly obtain consent and include him or her, and subsequently inform and recruit the clinician. The patient, the next-of-kin and the clinician will be included if the whole triad consents to participate. At the time of submission of this manuscript, the units were just about to begin recruiting participants to the triadic sub-study.

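### The registry, record and cost windows start at an undated inclusion that only in the intervention arm depends on ACP having been held, so the index stay may be split differently by arm

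*Protocol article*

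**What the plan says.** Three sections of the protocol article, and the matching rows of Table 1, use the same time origin.

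- Health economics: "Resource use and healthcare utilization will be summarized over 18 months prior to inclusion in the trial and 18 months after".
- Data from patient health records: "We will collect documentation from 18 months before to 18 months after inclusion (or until death) on the following", followed by a list that begins with ACP and similar conversations.
- Data from national registries: the same 18 months either side of inclusion, or until death.

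The Recruitment section says what completes inclusion: "The patient, the next-of-kin and the clinician will be included if the whole triad consents to participate". It describes one sequence for both arms: patients who meet the criteria are informed and asked for consent, then the relative, and last the clinician.

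The criteria differ by arm. Under Exclusion criteria for patients, an intervention patient is excluded if no ACP with patient, relative and physician was held before discharge, or if the clinician who took part in it has not consented. A control patient is excluded if patient or relative could not have taken part in ACP during the stay, or if no attending clinician has consented. The section on health care professionals adds that the intervention-arm clinician should be the one who participated in the ACP.

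On the use of the windows, Health economics says "we will use regression analysis to estimate the effect of ACP on total costs". For cost-effectiveness it says "The costs will include intervention costs of ACP and the cost of the hospital stay".

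**The concern.** All patients are acute inpatients, so a window that opens at inclusion can cut the index admission in two: bed-days before inclusion count as prior use, bed-days after it as follow-up use. That is harmless if the cut falls at a comparable point in both arms. Here the event that settles eligibility exists in one arm only, so comparability is not assured.

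Acute bed-days are likely to be among the costliest days in the window. If the cut came later in the intervention arm, index bed-days would leave its follow-up window and enter its prior window, and costs after inclusion would look lower with ACP even if ACP had no effect. If the cut came later in the control arm, the reverse would happen. The article intends to read lower costs as a possible sign of overutilization without ACP, so such a shift could be given a substantive interpretation.

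The record review has a related problem. If inclusion follows ACP, the index ACP conversation is itself documented before inclusion.

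**Working it through.** The plan gives no figure on this point to reproduce. The check is a comparison of the text, followed by arithmetic on assumed inputs.

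**Step 1: is the origin the same in both arms?**

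| Element | Intervention arm | Control arm |
|---|---|---|
| Window origin | Inclusion | Inclusion |
| What completes inclusion | Consent of the whole triad | Consent of the whole triad |
| ACP criterion | ACP must have been held before discharge | ACP would have been possible |
| Clinician | The one who took part in the ACP | An attending clinician |
| Date of inclusion | Not stated | Not stated |

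Recruitment approaches patients who already meet the criteria and recruits the clinician last. In the intervention arm, eligibility is final only once ACP has been held, and the clinician is identified by it. The natural reading is inclusion at or after ACP in that arm. Nothing comparable fixes the point in the control arm.

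**Step 2: how much could move?**

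All inputs are assumptions except the 18 months:

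- d = days by which inclusion comes later in the intervention arm, 1 to 5, all within the index stay;
- T = mean total cost after inclusion, in units of one index bed-day, 20 to 80;
- window = 18 × 30.4375 = 547.9 days.

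The later-included arm loses d index bed-days from its follow-up window and gains d average days at the end of it:

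shift = −d + d × T / 547.9

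| d | T = 20 | T = 40 | T = 80 |
|---|---|---|---|
| 1 | −0.96 (−4.8%) | −0.93 (−2.3%) | −0.85 (−1.1%) |
| 3 | −2.89 (−14.5%) | −2.78 (−7.0%) | −2.56 (−3.2%) |
| 5 | −4.82 (−24.1%) | −4.63 (−11.6%) | −4.27 (−5.3%) |

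Percentages are of T. Example: −3 + 3 × 40 / 547.9 = −2.78, and −2.78 / 40 = −7.0%. If controls are the ones included later, d is negative and every sign reverses.

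**Step 3: which comparisons are exposed?**

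- A follow-up total takes the shift once.
- A follow-up-minus-prior change takes it about twice, since d bed-days leave one window and enter the other (d = 3 gives about 6).
- The two windows added together are almost unaffected, since −d + d = 0 apart from the small end terms.

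**Step 4: scale against precision.**

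Take 210 patients per arm (35 × 6), borrow the plan's ICC of 0.05, giving a design effect of 1 + 34 × 0.05 = 2.7, and assume a cost coefficient of variation of 1. The detectable difference at 80% power is (1.96 + 0.84) × √(2 × 2.7 / 210) = 0.45 SD. The middle case (d = 3, T = 40) is 0.07 SD, about 15% of that. Across the table the range is about 2% to 54%.

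**The case against.** The strongest reply is that no section dates inclusion or orders it relative to ACP. The ACP items are exclusion criteria, and they would also fit a practice in which consent is taken early and the triad is dropped if ACP does not happen. Controls may be included late too: they need the same three consents, and patient and relative questionnaires in both arms cover "satisfaction with arrival, stay, and discharge at the hospital". A reader might infer that intervention patients are in fact included later in the stay than controls and that the analysis will therefore show a spurious saving. The documents do not support that. Both the lag and its direction are unknown, and this part of the objection stands.

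It also stands that the article does not say an admission will be cut into bed-days, that the total costs in the regression are not said to be follow-up costs only, and that the cost-effectiveness ratio may escape because the hospital stay is costed as its own item.

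It could further be said that allocating an index admission to windows is a matter for the analysis plan. That holds for a detail left open. Here the article has chosen an origin, and it is tied to ACP delivery in one arm only; an analysis plan that followed it would inherit the problem.

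Finally, an admission anchor is not neutral. Requiring ACP before discharge may select longer stays in the intervention arm, and the whole of those stays would then count in its costs. This is a fair point and shapes the fix.

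**Conclusion.** The point holds as a weakness in the stated time origin. Inclusion is undated, and only in the intervention arm does it depend on ACP having been held, so the origin is not the same in both arms and the index stay may be divided differently. That puts at risk the 18-month utilization summaries and any post-inclusion or pre/post cost comparison, including the total-cost regression if it uses those windows. The incremental cost-effectiveness ratio may be unaffected.

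The documents establish neither that a difference in timing will occur nor its size. Under the assumed lag of 1 to 5 days, about 1 to 5 bed-days per patient would cross the cut, or 1% to 24% of follow-up cost for T between 80 and 20. These percentages illustrate the exposure and are not an estimate. The health economic analysis serves a secondary objective. The change is worth making because it is cheap and removes the arm-dependent cut.

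**What to change.** In Data from patient health records, Data from national registries, Health economics and the matching rows of Table 1:

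1. Define time zero in both arms as the date of the index hospital admission, with windows of 18 months before it and 18 months from it.
2. Count the whole index stay in the window that starts at admission.
3. Report use and costs of the index stay separately from use and costs after discharge, by arm.
4. Keep the date of inclusion, and in the intervention arm the date of ACP, as recorded variables, so that the timing can be described.

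The cost is mainly wording, and no power is lost. The admission date should be available from the patient records or the linked Norwegian Patient Registry; this is a reasonable expectation, though the article does not say so. The linkage must reach back slightly further, to 18 months before admission.

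There is one small downside. Any selection of longer stays through the ACP-before-discharge criterion will enter the index-stay component for the intervention arm. A common anchor does not remove that selection; item 3 makes it visible and keeps it apart from the post-discharge comparison.
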